### 2.8. Interventions

#### 2.8.1. Web-Based Physical–Cognitive Telerehabilitation Exergaming

Participants will perform a physical–cognitive exergame via ExerbrainCMU web-based platform at home setting for 60 min/session, 3 sessions/week for 12 weeks. The program will consist of warm-up, physical–cognitive training, and followed by cool-down. The physical–cognitive exergame will consist of trunk exercises, upper- and lower-extremity exercises, exercises using Proprioceptive Neuromuscular Facilitation (PNF) patterns, balance exercises, aerobic exercises, sit-to-stand training, and side-walking exercises, combined with cognitive training targeting executive function, attention, memory, visuospatial ability, and dual-task performance. In general, physical–cognitive exergames will mostly be performed in a sitting position. Task difficulty will be progressively increased by manipulating movement complexity, speed, and directional demands, while cognitive load will be adjusted by varying cognitive complexity, the number of stimuli, task conditions, attentional demand, and memory load. The intervention will comprise three difficulty levels: easy (weeks 1–4), medium (weeks 5–8), and hard (weeks 9–12). Participants scoring below 80% across all games will be required to repeat the current level until the 80% passing criterion is met before progressing to the next level. Instructional materials, including basic instructions and training videos, will be provided to ensure correct and safe execution of the intervention. A summary of the intervention is presented in Figure 2 and Table S2 (Supplementary Materials).

Telerehabilitation will be conducted using the ExerbrainCMU web-based platform. Participants will engage in exercise training at home or in remote areas via simultaneous video conferencing, accompanied by a physiotherapist. The telerehabilitation system consists of a main monitoring controller for physiotherapists, a network data system, and connected end-users who are stroke patients. The main monitoring controller enables therapists to monitor exercise accuracy and safety at weeks 2, 4, 8, 10, and 12. Family members or caregivers may stand beside participants if there are safety concerns.

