#### 2.8.2. Control Condition

Participants in the control group will continue their usual lifestyle or receive usual care rehabilitation during the study period, with no additional intervention. They will be encouraged to maintain their usual activities and avoid participation in other structured exercise programs outside the study intervention. The type, frequency, and intensity of concurrent treatments will be recorded and treated as covariates in the statistical analysis to control for potential confounding effects. After the 12-week period, they will be invited to participate in the intervention program according to their preference. Participants will be asked to inform the research team if there are any routine changes or unexpected events (e.g., hospital admission, illness).

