### 2.9. Intervention Adherence and Adverse Events

Participants in the intervention program will have their training sessions automatically recorded on the ExerbrainCMU web-based platform immediately after each exercise session, including information on session duration, training completion, and training frequency. These data will be used to monitor adherence and engagement throughout the intervention period. Weekly reminders will be sent via social media applications (e.g., LINE and Facebook) to promote adherence. In addition, research staff will conduct scheduled telemonitoring sessions at weeks 2, 4, 8, 10, and 12, during which information regarding participants’ training will be collected and cross-validated with the platform records.

Participants will be instructed to report any adverse events that occur during the study. They will also be asked about any health problems at each assessment point from baseline to 12 weeks. Participants will be informed that they can contact the research team at any time if they have questions or concerns. All adverse events or harms associated with the intervention will be recorded and reported in the study findings.

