Motor function, gait speed, balance and limits of stability, muscle power, and weight distribution will be assessed using the Motor Assessment Scale (MAS) [44], 10-Meter Walk test (10MWT) [45], the Modified Functional Reach Test (MFRT) [46,47], 5 times sit-to-stand test (5TSTS) [48], and the Stance Symmetry Test (SST) [49], respectively. For the MAS test, participants will be asked to perform 8 items of functional tasks: supine to side lying, supine to sitting, balance sitting, sitting to standing, walking, upper arm function, hand movement, and advanced hand activities. Each item is scored on a 7-point scale (0–6; 0 = no function to 6 = normal function), based on a person’s ability to perform specific tasks. Participants will perform each task three times and the best performance will be recorded. For the 10MWT, participants will be instructed to complete a 10 m walk at a self-selected speed with or without walking aids [45]. An acceleration distance of 2 m and a deceleration distance of 2 m will set up at the beginning and the rear end. The time will be recorded by digital stopwatch for the middle 10 m distance. Measurements will be determined twice. The speed will be calculated by dividing the distance by time (m/s). Dynamic balance and limits of stability while sitting will be measured by MFRT [46]. Participants will be sitting on a standard chair with their feet shoulder-width apart, flat on the floor, hips and knees at 90° flexion with the non-paretic side closest to the wall. The participant will be instructed to reach as far as possible with the arm horizontal while maintaining balance. The location of the fifth finger at the beginning and the end of the reach will be recorded. MFRT will consist of three conditions including forward reach while sitting with the unaffected side near the wall, lateral reach to the right while sitting with the back to the wall, and lateral reach to the left while sitting with the back to the wall. Each participant will perform a total of five trials per condition. The first two trials will be used for familiarization, and the mean of the final three trials will be used for analysis [46,47]. As for muscle power, participants will be instructed to perform five sit-to-stand repetitions as quickly as possible. The time required to complete the task will be recorded [48]. Weight distribution will be measured using the SST. This test assesses the distribution of weight between both legs. Participants will be instructed to stand with each foot on a separate weighing scale, with the distance between the feet set at 11% of the participant’s height. They will be asked to stand as still as possible for 30 s. The assessors will record the weight borne by each leg at 25 s. Each participant will complete three trials, and the results will be averaged. The symmetry ratio will be calculated as the average weight bearing through the affected leg divided by the average weight bearing through the non-affected leg [49]. Furthermore, minimum detectable difference (MDD) values for the MFRT, 5TSTS, and SST will be used to aid the interpretation of clinical significance. Body fat percentage and fat mass will be measured using a body fat composition monitor with an accuracy of 0.1 kg and 0.1%, respectively [50,51]. In addition, the Physical Activity Enjoyment Scale (PACES) will be used to assess participants’ enjoyment during the intervention [52]. PACES consists of eight items rated on a 7-point Likert scale from 1 (strongly disagree) to 7 (strongly agree). The overall enjoyment score will be derived from the sum of all item scores. Furthermore, adherence to the intervention will be recorded and calculated as the percentage of attended physical–cognitive training sessions using (n/36) × 100.

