
### 2.11. Statistical Analyses

Descriptive statistics will be used to summarize the demographic data and baseline characteristics of each group. Data normality will be assessed using the Kolmogorov–Smirnov test. Homogeneity of variances will be evaluated using Levene’s test. Independent-samples *t*-tests and chi-square tests will be used to compare demographic characteristics between the intervention and control groups. The primary analysis will be conducted using a two-way mixed-model ANOVA to examine differences in outcome measures between groups across two assessment time points (baseline and 12 weeks). The Bonferroni correction will be used for the post hoc analysis. In case of baseline imbalances, an analysis of covariance (ANCOVA) will be conducted to compare post-intervention outcome measures between groups, with baseline scores and time since stroke included as covariates to control for potential confounding effects. However, if data are not normally distributed, appropriate nonparametric methods will be considered. The primary comparative analyses will follow the intention-to-treat principle. Missing data will be handled using multiple imputation by chained equations, generating five imputed datasets. The imputation model will include all outcome variables, baseline scores, and relevant covariates. Additionally, a per-protocol analysis will be performed for the primary outcomes to evaluate the intervention effects among participants who attended at least 80% of the sessions. Statistical significance will be set at *p* < 0.05.

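### The per-protocol rule of at least 80% attendance cannot be applied to controls, so the supportive analysis of both primary outcomes has no randomised comparison

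*Protocol article*

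**What the plan says.** Section 2.11 makes the intention-to-treat comparison primary, with multiple imputation. It then adds a per-protocol analysis, for the primary outcomes only, to "evaluate the intervention effects among participants who attended at least 80% of the sessions". This is the only criterion given for the per-protocol set.

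The other sections settle whose sessions these are:

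- Section 2.8.1 schedules the exergame at "60 min/session, 3 sessions/week for 12 weeks", which is 36 sessions.
- Section 2.10.2 defines adherence on that denominator: "calculated as the percentage of attended physical–cognitive training sessions using (n/36) × 100".
- Section 2.9 logs attendance for one arm: "Participants in the intervention program will have their training sessions automatically recorded on the ExerbrainCMU web-based platform".
- Section 2.8.2 says that controls "will continue their usual lifestyle or receive usual care rehabilitation during the study period, with no additional intervention". They get access only later: "After the 12-week period, they will be invited to participate in the intervention program according to their preference".

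**The concern.** A per-protocol set needs a rule that can be applied in both arms. This one depends on a behaviour that exists in one arm only and is observed after randomisation. Either the analysis cannot be run, or it trims the intervention arm and leaves the control arm untouched. In the second case, the controls who would not have kept up stay in, while their counterparts in the intervention arm are removed.

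The analysis covers both primary outcomes, executive function and fall risk, and carries no exploratory label. If it came out stronger than the intention-to-treat result, it could be read as evidence that more training gives more benefit, when part or all of the gap might come from who attends.

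**Working it through.** **1. Can the rule be applied?** 3 sessions × 12 weeks = 36, and 0.80 × 36 = 28.8, so the threshold is 29 of 36 sessions. A control has 0 available sessions before week 12. No control qualifies, and Section 2.11 gives no control-side criterion.

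**2. What would the trimmed comparison show with no true effect?** Two quantities are needed that the documents do not give, so both are assumptions:

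- q, the fraction of the intervention arm reaching the threshold
- r, the correlation of attendance with the quantity analysed

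If the top fraction q on a normal attendance scale is kept and all controls are kept, the expected difference in SD units is r × φ(z)/q, where z is the (1 − q) quantile of the standard normal. At q = 0.7, z = −0.524, φ(z) = 0.348 and φ(z)/q = 0.497.

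| q | r = −0.3 | r = 0 | r = 0.3 | r = 0.5 |
|---|---|---|---|---|
| 0.9 | −0.06 | 0 | 0.06 | 0.10 |
| 0.8 | −0.10 | 0 | 0.10 | 0.17 |
| 0.7 | −0.15 | 0 | 0.15 | 0.25 |
| 0.5 | −0.24 | 0 | 0.24 | 0.40 |

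A simulated t-test with 26 allocated per arm and no true effect (20,000 runs) was significant in favour of the intervention in 6.9% (r = 0.3) and 12.4% (r = 0.5) of runs at q = 0.7. At q = 0.8 the figures were 5.1% and 8.3%. The nominal rate is 2.5%.

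**3. Which r matters under the planned model?** With two time points, the group-by-time term of the mixed ANOVA compares mean changes. The fallback ANCOVA compares follow-up adjusted for baseline. So r must be the correlation of attendance with change, or with baseline-adjusted outcome, and not with the level at 12 weeks.

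Suppose attendance reflects only stable prognosis, with the same correlation r to baseline and to follow-up, and let ρ be the baseline–follow-up correlation (assumed 0.5 to 0.8). At q = 0.7:

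- Change score: 0.497 × (r − r) = 0.
- ANCOVA, approximately r × (1 − ρ) × 0.497:
  - r = 0.3, ρ = 0.8: 0.03
  - r = 0.5, ρ = 0.8: 0.05
  - r = 0.3, ρ = 0.5: 0.07
  - r = 0.5, ρ = 0.5: 0.12

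The fitted ANCOVA gives 0.13 in the last case, because trimming one arm flattens the pooled slope from 0.50 to 0.47 and 0.248 × (1 − 0.472) = 0.131.

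**4. Against what effect?** Section 2.5 gives 0.46 for executive function and 0.57 for fall risk. Read as Cohen's f, a between-groups repeated-measures calculation (two measurements, correlation 0.5 assumed) gives totals of 30 and 22, against the stated 30 and 20. With d = 2f, the anticipated effects are 0.92 and 1.14 SD. The value 0.37 in the same section belongs to gait speed, a secondary outcome outside the per-protocol analysis.

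**The case against.** The strongest reply has four parts.

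*The analysis is supplementary.* This stands. Intention-to-treat is primary, no decision rule hangs on the per-protocol result, and no primary conclusion depends on it.

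*A condensed article may leave the control-side definition to an analysis plan.* This stands in part. That the article is silent on how controls enter is not in itself a fault. But it does state a criterion and the aim of estimating intervention effects, and that criterion cannot serve that aim. Adding that all controls are kept would make the analysis runnable but would not restore the randomised comparison.

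*The direction is not shown.* A reader might infer that the analysis must favour the intervention and will look stronger than intention-to-treat. The documents do not support that certainty. They report neither an adherence rate nor a correlation of attendance with outcome, and the bias is zero at r = 0 and negative at r < 0. A positive sign is still the reasonable expectation. The Introduction lists low motivation, health concerns and stroke-related impairments as barriers to continuing activity, and Section 2.8.2 foresees illness and hospital admission during the study. Such events would lower attendance and worsen 12-week performance together.

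*The planned model uses baseline.* This stands as a limit on size. A reader might take 0.15 to 0.25 SD as the expected bias, but those figures need attendance to predict change at 0.3 to 0.5. Selection on stable fitness or motivation alone largely cancels. Baseline does not remove selection through events during the 12 weeks.

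**Conclusion.** The point holds as a fault in the supportive analysis only. The attendance rule cannot be applied to controls, and the only workable reading, adherers against all controls, is an inference that breaks the randomised comparison for both primary outcomes.

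The bias probably favours the intervention. Its size cannot be derived from the documents. With 70% adherence assumed, it runs from about 0 (change scores) or 0.03 to 0.13 SD (ANCOVA) under stable prognosis, to 0.15 to 0.25 SD if attendance predicts change at 0.3 to 0.5. Anticipated effects are 0.92 and 1.14 SD if the stated values are Cohen's f, so selection of this size would not by itself produce an effect as large as planned for. It could still widen the gap between the supportive and the primary result. The plan should be changed, but the validity of the primary analysis is not in question.

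**What to change.** Make the supportive adherence analysis a complier-average estimate for both primary outcomes: two-stage least squares with randomised group as instrument, sessions attended/36 as exposure (0 for controls) and the baseline score as covariate. Controls have no access before week 12, so non-compliance is one-sided. Without covariates the estimate equals the intention-to-treat difference divided by the mean exposure in the intervention arm.

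Do not use reaching 29 of 36 sessions as a yes/no exposure. It counts someone who attended 20 sessions as untreated and inflates any true effect: at 70% adherence the intention-to-treat difference would be multiplied by 1/0.7 = 1.43.

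If the 80% comparison is kept, show it as descriptive, and state that all controls are retained and that it is open to adherence selection.

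The cost is a few lines of analysis on attendance data that the platform already records. The downsides are a wider interval than intention-to-treat and two assumptions to be declared: that allocation acts only through sessions attended, and that benefit is proportional to sessions.

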### 2.12. Artificial Intelligence Statement

During the preparation of this manuscript, the authors used ChatGPT (GPT-5.3-mini) to assist with language editing to improve clarity and readability. No content generation was performed using artificial intelligence. The authors carefully reviewed and edited the content and take full responsibility for the final version of the manuscript.

## 3. Discussion

The present work describes the study protocol of an RCT designed to evaluate the effectiveness of web-based physical–cognitive telerehabilitation exergaming on physical and cognitive performance in chronic stroke survivors. To our knowledge, this is the first RCT protocol to investigate the effectiveness of physical–cognitive training delivered via web-based telerehabilitation exergaming across a comprehensive range of domains, including motor function, gait speed, balance and limits of stability, fall risk, muscle power, and weight distribution, as well as global cognitive function, executive function, memory, and attention in individuals with chronic stroke. As research evidence has demonstrated the benefits of physical–cognitive training on health outcomes, it is proposed that web-based physical–cognitive telerehabilitation exergaming may further enhance both physical and cognitive functions beyond the effects of usual care. In addition to the accessibility and other advantages of digital technology, a home-based intervention delivered through web-based telerehabilitation exergaming with individualized training progression may improve adherence and provide a feasible and enjoyable intervention.

Given the long-term and chronic nature of stroke-related impairments, sustained engagement in physical activity and rehabilitation is essential to optimize and maintain long-term functional outcomes. However, access to rehabilitation services is often limited by geographical, financial, and logistical barriers, particularly for individuals living in the community after hospital discharge. Web-based telerehabilitation may address these challenges by enabling continuous, home-based training while reducing the burden associated with travel and service availability. Within this context, the present study protocol provides a rigorous framework for evaluating the clinical effectiveness of a web-based physical–cognitive telerehabilitation exergaming intervention. The findings from the planned RCT will contribute important evidence regarding the potential of digitally delivered, home-based rehabilitation to enhance physical and cognitive outcomes in chronic stroke survivors. If proven effective, this intervention may support the development of scalable and accessible rehabilitation models that complement usual care and inform future clinical practice and health service delivery. Remote delivery via telerehabilitation may bridge gaps in healthcare access caused by geographic distances. The novel web-based physical–cognitive telerehabilitation exergaming may contribute to clinical applications and promote therapeutic outcomes for chronic stroke survivors.

There are some limitations to this study. First, to control for potential spontaneous recovery effects, all participants will be recruited exclusively from the chronic stage of stroke. Therefore, the study findings may not be generalizable to individuals in the acute or subacute stages. Second, participation in the present study is limited to individuals who are regular users of a mobile phone, tablet, or notebook computer, which may introduce selection bias. In addition, this may also contribute to digital inequality, as not all patients have equal access to the internet or possess the necessary digital literacy to engage with the intervention. Lastly, as this study focuses on short- to medium-term outcomes following 12 weeks of training, the long-term sustainability of the intervention effects will require further investigation.

## Figures and Tables

**Figure 1 jcm-15-02945-f001:**
[figure not shown]
Flow chart of the study procedure.

**Figure 2 jcm-15-02945-f002:**
[figure not shown]
Summary of the characteristics of web-based physical–cognitive telerehabilitation exergaming.

**Table 1 jcm-15-02945-t001:** Schedule of enrolment, interventions, and assessments.

Timepoint	Study Period			
	Enrolment	Allocation	Post-Allocation	Follow-Up
	−t_1_	t_0_	0–12 Weeks	t_2_ 12 Weeks
Enrolment:				
Eligibility screen	X			
Informed consent	X			
Allocation		X		
Interventions:				
Intervention group				
Control group				
Assessments and Measurements:				
TMT		X		X
TUG		X		X
10MWT		X		X
MoCA test		X		X
Digit Span Test		X		X
MAS		X		X
MFRT		X		X
5TSTS		X		X
SST		X		X
Body composition		X		X
PACES			X (after 1 week)	X

Note. TMT: Trail Making Test; TUG: Timed Up and Go test; 10MWT: 10-Meter Walk Test; MoCA: Montreal Cognitive Assessment; MAS: Motor Assessment Scale; MFRT: Modified Functional Reach Test; 5TSTS: 5 Times Sit-To-Stand test; SST: Stance Symmetry Test; PACES: Physical Activity Enjoyment Scale. X indicates that the assessment was performed at that timepoint.

## Data Availability

No new data were created or analyzed in this study.

## Abbreviations

The following abbreviations are used in this manuscript:

TMT	Trail Making Test
TUG	Timed Up and Go test
10MWT	10-Meter Walk Test
MoCA	Montreal Cognitive Assessment
MAS	Motor Assessment Scale
MFRT	Modified Functional Reach Test
5TSTS	5 Times Sit-To-Stand test
SST	Stance Symmetry Test
PACES	Physical Activity Enjoyment Scale
